#### Secondary Outcomes

##### Changes in AF Knowledge

The Jessa Atrial Fibrillation Knowledge Questionnaire (JAKQ) is a 16-item scale used to assess the knowledge of patients’ AF about the arrhythmia illness [4]. For every item, false responses or “I don’t know” responses are scored as 0, and the correct responses are scored as 1. The total score of the scale is calculated by adding up all item scores.

##### Measurement of Vital Parameters

Clinical data on weight, blood pressure, pulse, steps, sleep, and ECG in the intervention group will be collected as specified in Table 1.

##### Changes in Anxiety and Depression

Symptoms of anxiety and depression are measured using the Hospital Anxiety and Depression Scale (HADS) [35]. The HADS is a 14-item self-reported questionnaire often used for screening of psychological distress in patients with cardiac conditions. Each item is scored on a 4-point Likert scale ranging from 0 to 3. The 2 subscales, anxiety and depression, each comprise 7 items, and scores on these subscales range from 0 to 21, with higher scores indicating higher levels of anxiety or depressive symptoms.

##### Changes in Motivation

Motivation is measured by the Health-Care Self-Determination Theory Questionnaire Packet (HC-SDTQ). The HC-SDTQ includes 3 separate questionnaires: the Treatment Self-Regulation Questionnaire, which focuses on autonomy as stipulated by SDT [36]; the Perceived Competence Scale, which assesses patients’ sense of competence about engaging in, or maintaining, a healthier behavior [37]; and the Health Care Climate Questionnaire, which assesses the patient’s perception of autonomy support from their health care provider [38].

##### Burden of AF

The burden of AF is measured using the Arrhythmia-Specific Questionnaire in Tachycardia and Arrhythmia (ASTA) [39]. The ASTA measures symptoms and HRQoL in patients with different forms of arrhythmias, including AF. The ASTA is divided into 3 parts: Part I assesses demographic data, such as the most recent episode of arrhythmia, current medication, and the presence of arrhythmia at the time of follow-up; Part II measures the arrhythmia-specific symptom burden; and Part III measures HRQoL. Parts II and III are scored using a 4-point Likert-type scale (0=“No” to 3=“Yes, a lot”). The total score range is from 0 to 100, with a higher score indicating a higher symptom burden or a negative effect on HRQoL.

##### Use of HeartPortal

Time log files for login and logout of patients and relatives will be analyzed in order to identify which parts of the HeartPortal are being used and for how long. The patients will be asked for their consent prior to extracting their log files from the database for analysis.

##### Perspectives and Experiences From Participating in the FP-AF Program

Participant-observation [40,41] will be used in situations such as educating and counseling the patients and relatives in using the technologies at home and to observe how patients and relatives use the digital technologies and the HeartPortal.

Perspectives and experiences of patients, relatives, and HPs participating in the FP-AF program will be explored using semistructured qualitative interviews, inspired by Brinkmann and Kvale [42]. Interviews will be performed until data saturation is reached, with a minimum of 10 interviews conducted for each group: patients, relatives, and HPs. The interviews will be recorded, transcribed, and analyzed in themes inspired by Brinkmann and Kvale [42] and based on their phenomenological approach. The interviews will be coded by 2 researchers using NVivo (version 14.0) software [43].

##### Cost-Effectiveness Evaluation

Throughout the duration of the study, we will also collect information on unplanned admissions for any reason with at least 1 overnight stay, unplanned readmissions for any reason and length of stay, visits to outpatient clinics, rehabilitation activities, visits to the general practitioner, equipment used, driving distance, personnel use, and numbers of phone or video calls. The analysis will be based on the guidelines for economic evaluation elaborated by Drummond et al [44].

### Data Storage

Demographic data are being stored within the Future Patient database, and the questionnaire data are stored in the REDCap (Research Electronic Data Capture; Vanderbilt University) software for quantitative analysis.

### Adverse Events, Dropout, and Technical Issues

All adverse events, dropouts, and deaths, as well as any technical issues related to the equipment, will be registered. No preterm study stop criteria are planned.

### Data Analysis

#### Statistical Analysis

Baseline characteristics will be presented as frequencies and percentages or as medians and IQRs, as appropriate, and the data will be stratified by randomization groups and by sex. Changes over time on the primary outcome will be analyzed in accordance with the intention-to-treat principle, using a mixed-effects model for repeated measures design with robust variance in order to relax the assumption of normally distributed residuals. In addition, margin plots will be produced in order to investigate the interaction of time and randomization group. A sensitivity analysis will be conducted in order to investigate the effects of missing data as a result of dropout by comparing baseline characteristics between complete cases and dropouts, followed by adjusted analyses of the primary outcome using appropriate baseline characteristics as adjustment parameters. Secondary outcomes will be analyzed in a manner similar to the primary outcome. We will also examine overlaps between and variations within groups of different sexes. In examining sex differences, we will adjust for possible confounding factors (eg, age).

#### Trends and Patterns in Multiparametric Clinical Data

Data will be analyzed in order to identify correlations in multiparametric data collected during the 4 months. Initial analysis of the multiparametric data will be carried out by assessing the architectural structures and complexities of the data design through basic statistical and distributive analysis. Differences in the multiparametric data between baseline and postintervention measurements will be tested with paired *t* tests. Correlations of multiparametric data will be compared with patient-reported symptoms of AF. Paired *t* tests will be performed for the multiparametric data between periods both with and without patient-reported symptoms of AF in patients experiencing symptoms. Also, *t* tests will be performed for multiparametric data between patients with and without symptoms of AF. Simplistic features will be developed based on the statistical analyses and correlations between data.

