**Figure 2 figure2:**
[figure not shown]
The context of the Future Patient program.

Four elements of HeartPortal.A platform containing atrial fibrillation and rehabilitation related information pages (text, images or illustrations, animation, link to other validated sources, etc).Visualization of measured values (steps, weight, pulse, blood pressure, and sleep) in graphs that offer an easy overview and trends in data.A communication platform (video and chat) that enables patients to communicate directly with health care professionals. Video consultations will be conducted at 1 month and 4 months after enrollment in the study and additionally as needed on an individual basis.A rehabilitation plan. For each patient, an individualized rehabilitation plan is defined in a dialogue between the patient, the doctor, and a project nurse. The rehabilitation plan is formulated using individual parameters such as weight, physical status, pulse, and blood pressure. The patients write down their personal rehabilitation goals on the HeartPortal. The patients start the rehabilitation plan at the time of enrollment in the study. A project nurse monitors the patient’s data twice a week and contacts the patients if the rehabilitation goals have not been met, data have not been transmitted to the HeartPortal, or in case data are not within the normal range set for the patient.

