Technologies used in the cardiac telerehabilitation group.Blood pressure monitor (iHealth Neo [BP5S]) [28]. Measurement of systolic and diastolic pressure and pulse. Connects to an app on the tablet to record the measurement and the tablet’s internet connection to transfer the measured values. Blood pressure is measured twice a week.Weight scale (iHealth Lina) [29]. Allows the patient to follow his or her weight and observe weight loss or gain. Connects to an app on the tablet to record the weight, and the tablet’s internet connection transfers the measured values to the HeartPortal. Weight is measured twice a week.Activity tracker (Fitbit Inspire 3|Health & Fitness Tracker) [30]. Measures physical activity, counted as steps and calories burned as well as pulse throughout the day. The activity tracker can also measure sleep if worn while sleeping. An app on the tablet is used for viewing and reviewing the tracked data and for data transfer. Activity, measured as steps, is measured every day and transmitted to the HeartPortal.Electrocardiography (ECG) monitor (KardiaMobile) [31]. Consists of a small device with touchpads, one for each hand. The monitor uses ultrasound to communicate with an app on the tablet. The app transfers the data to a General Data Protection Regulation-compliant system for clinicians, KardiaPro. ECG is carried out twice a week. The Kardia device includes an artificial intelligence–powered algorithm with an accuracy rate of 97% [31]. When patients measure their ECG, the device detects their heart rhythm. Patients have also been taught to interpret the results, such as the difference between sinus rhythm and AF.Sleep sensor (Emfit QS) [32]. Monitors pulse and respiration during sleep, sleep duration, stages, and sleep quality. Sleep is measured in hours every night, and the sensor data are transmitted to the HeartPortal.Video solution (VDX, Medcom) [33], a national video platform in Denmark within health care.

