**Secondary**									
	Changes in AF knowledge	(I,C)				(I,C)		(I,C)	
	*Measurement of vital parameters*								
	Weight	(I,C)		(I)	(I)				
	Blood pressure	(I,C)		(I)	(I)				
	Pulse	(I,C)	(I)		(I)				
	Steps	(I)	(I)			(I)		(I)	
	Sleep	(I)	(I)						
	Electrocardiogram	(I,C)		(I)	(I)				
	Changes in anxiety and depression	(I,C)				(I,C)		(I,C)	
	Changes in motivation	(I,C)				(I,C)		(I,C)	
	Burden of AF	(I,C)				(I,C)		(I,C)	
	Use of HeartPortal					(I)			
	Patients’ and relatives’ perspective and experiences					(I)			
	Health care professionals’ perspective and experiences					(I)			
	Cost-effectiveness evaluation					(I,C)		(I,C)	
	Trends and patterns in multi-parametric clinical data					(I)			

^a^AF: atrial fibrillation.

^b^I***:*** intervention group.

^c^C: control group.

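### The change in monitored vital data is assigned two different analyses, and the paired t test loses patients without an end-of-program reading or mixes their exposure times

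*Protocol article*

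**What the plan says.** The section Trends and Patterns in Multiparametric Clinical Data sets out to "identify correlations in multiparametric data collected during the 4 months" and then fixes the test for change: "Differences in the multiparametric data between baseline and postintervention measurements will be tested with paired" t tests. It does not say which reading or period counts as postintervention.

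The Statistical Analysis section gives the primary outcome a mixed-effects repeated-measures model with robust variance under intention to treat, and adds: "Secondary outcomes will be analyzed in a manner similar to the primary outcome". Two rows of Table 1 bring the monitored data under that sentence, because both stand in the secondary block: "Measurement of vital parameters" and "Trends and patterns in multi-parametric clinical data".

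The section Measurement of Vital Parameters refers to the table for timing: "Clinical data on weight, blood pressure, pulse, steps, sleep, and ECG in the intervention group will be collected as specified in Table 1". In the intervention arm, Table 1 schedules:

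- weight, blood pressure and ECG at baseline, twice a week and as needed;
- pulse at baseline, every day and as needed;
- sleep at baseline and every day;
- steps at baseline, every day, and at 4 and 7 months.

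The textbox on technologies agrees, for example "Weight is measured twice a week". The textbox on the HeartPortal foresees gaps: the nurse contacts patients when "data have not been transmitted to the HeartPortal".

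**The concern.** Two methods are named for the same data, and they differ in whom they analyze. A mixed model keeps every patient with any reading. A paired t test keeps only patients with both values. For five of the six parameters the second value has no visit of its own, so it depends on a rule that the article does not state.

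Two rules are possible, and each has a cost. If a reading near month 4 is required, patients who drop out or stop transmitting leave the test, and the result describes those who kept measuring. If the last available reading is used, they stay, but a patient who stopped early contributes a change over a shorter exposure. Choosing between the methods, or between the rules, after the data have been seen would also leave room for selective reporting.

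ECG raises a further difficulty. The textbox on technologies says that the device detects heart rhythm and that patients are taught to tell sinus rhythm from AF. A t test on one yes/no rhythm result at each end is a poor fit.

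**Working it through.** **The plan's own figure.** The article gives no figure for the paired tests. Its only sample-size figure concerns the primary outcome. With a difference of 11, SD 23, 90% power and two-sided alpha 0.05 (alpha is my assumption), n per arm = 2 × (1.960 + 1.282)² × 23² / 11² = 91.9, rounded up to 92. That is 184 in total, as stated. It has no bearing on this point beyond supplying the 104 per arm and the 10% dropout used below.

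**Is an end value scheduled?** Four months is 4 × 365.25 / 12 / 7 = 17.4 weeks. Twice-weekly readings give 2 × 17.4 = about 35 per patient, and daily readings about 122. The monitoring module lasts 4 months, so readings near month 4 are planned. What is undefined is which of them form the end value.

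**Patients lost under a complete-pairs rule.** Pairs = 104 × (1 − d). The plan gives d = 10%. The other values are an assumed range, because the article gives no rate of non-transmission. The detectable change is (1.960 + 0.842) / √pairs, in SDs of the change (80% power, two-sided 0.05, normal approximation).

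| d | Pairs | Detectable change (SD) |
|---|---|---|
| 0% | 104 | 0.27 |
| 10% | 94 | 0.29 |
| 20% | 83 | 0.31 |
| 30% | 73 | 0.33 |

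At 10%, 104 × 0.10 = 10.4, so about 10 patients are lost. The cost in power is modest. The bias, if those who stop differ from those who continue, cannot be computed from the article.

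**Precision from averaging the end value.** The last 2 weeks hold 2 × 2 = 4 twice-weekly readings. Take one baseline reading and an end value averaged over k readings, with reading-to-reading SD σ and true-change SD τ. Then Var(change) = τ² + σ² + σ²/k. The article gives neither SD, so both are assumptions, in mmHg for blood pressure.

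- τ = σ = 10, n = 94, k = 1: √(100 + 100 + 100) = 17.32, and SE = 17.32 / √94 = 1.79.
- τ = σ = 10, n = 94, k = 4: √(100 + 100 + 25) = 15.00, and SE = 15.00 / √94 = 1.55, which is 13% smaller.
- Smallest gain in the range (τ = 15, σ = 5): √275 = 16.58 against √256.25 = 16.01, about 3%.
- Largest gain in the range (τ = 5, σ = 10): √225 = 15.00 against √150 = 12.25, about 18%.

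If the baseline were also an average of 4 readings, the variance at τ = σ = 10 would be 100 + 25 + 25 = 150, the SE 12.25 / √94 = 1.26, and the reduction 29%. Table 1 shows one scheduled baseline, so I do not use that figure.

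**The case against.** The strongest reply is that only a windowing rule is missing, and a journal article may leave that to the full protocol or analysis plan. I accept this for the definition of the end value taken alone. It does not cover the naming of two different methods for the same secondary outcomes, which the article itself states.

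It can also be said that the multiparametric section is a separate, exploratory analysis of the intervention arm. On that view the mixed-model sentence, which only asks for a similar manner, was never meant to govern it. That is a fair reading. But Table 1 places the trends row among the secondary outcomes and the article makes no exception for it, so the text needs a sentence either way.

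A reader might draw four stronger conclusions that the documents do not support:

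- **That no postintervention data exist for five parameters.** Daily or twice-weekly readings run to month 4, and the trends row is marked in the 4-month column.
- **That the gap in Table 1 leaves patients who stop transmitting without a pair.** A fixed 4-month entry would not give a dropout a value, and a last-available rule would. The nurse's contact may also reduce such gaps.
- **That most readings go unused.** A pair of single readings would leave out about 94% of twice-weekly values (1 − 2/35.8) and 98% of daily ones (1 − 2/122.75), but only in this test. The section also plans correlations with symptoms, comparisons of periods with and without symptoms, and derived features. Nor does it say that the pair consists of single readings.
- **That a mixed model is needed for precision.** The gain computed above comes from averaging, which a paired t test on window means would share. The case for the model rests on whom it keeps.

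**Conclusion.** The point holds in limited form. The article names a paired t test and a mixed-effects repeated-measures model for the same secondary outcomes and does not say which applies. The t test either omits patients without a late reading, about 10 of 104 at the stated dropout and more if others stop transmitting, or compares changes over unequal exposure.

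The measurable cost is small. The detectable change goes from 0.27 to 0.29 SD at 10% loss. Averaging four end readings would cut the SE by about 13% at the assumed SDs of 10 and 10, and by 3% to 18% over reading SD 5–10 and true-change SD 5–15. The size of any selection bias is unknown.

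This is a secondary analysis within the intervention arm. Except for steps and sleep, which controls do not have at all, controls have vital data only at baseline, so no randomized comparison is at stake and the primary outcome is untouched. Severity is low, but the remedy is cheap and the model is one the plan already names.

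**What to change.** In Trends and Patterns in Multiparametric Clinical Data, for the baseline-to-end change in the intervention arm:

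1. Replace the paired t tests with the mixed model with robust variance from the Statistical Analysis section, without the group terms. Fit it to the Table 1 baseline value and all in-program readings of every intervention patient.
2. Enter time as categories, for example by month with the last 2 weeks of month 4 as their own category, so that no linear trend is forced.
3. Report the change from the scheduled baseline to the last 2 weeks of month 4, and write end of program in place of postintervention.
4. For ECG rhythm, a yes/no result at each recording, use a repeated-measures model for a binary outcome.
5. State in one sentence that this model governs the vital parameters as secondary outcomes.

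The cost is wording and a somewhat more complex model. No new data are needed, because the readings are already collected. The model still assumes that data are missing at random, so it does not remove bias if patients stop transmitting for reasons that their recorded values do not reflect. The change should be made before these data are analyzed.

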#### Qualitative Analysis

A research assistant will transcribe all interviews into text files. Data will be coded in NVivo (version 14.0; QSR International), drawing inspiration from the SDT theoretical framework and using methods developed by Brinkmann and Kvale [42]. Two different researchers will be responsible for conducting the interviews and analyzing the data. The data will be presented in terms of key themes and major findings.

#### Economic Evaluations

A cost-effectiveness analysis of the FP-AF telerehabilitation program compared to conventional care will be made at 7 months after inclusion for both groups. The analysis will be based on the guidelines for economic evaluation elaborated by Drummond et al [44].

## Results

The findings of the RCT will be analyzed during the spring of 2025 and subsequently published in peer-reviewed journals in the fields of telerehabilitation, clinical cardiology, and health economics. In addition, these results will be presented at relevant international scientific conferences. A total of 208 patients will be enrolled, 104 in the telerehabilitation group and 104 in the control group.

The evaluation of the FP-AF program comprises both clinical data recorded by the patients and data gathered through interviews and questionnaires. The evaluation involves quantitative analysis of primary and secondary outcomes (questionnaires) as well as qualitative exploration of the perspectives and experiences of patients with AF, their relatives, and HPs. Finally, a health economic evaluation will be conducted. Taken together, the data and the associated analyses will provide a comprehensive perspective on the effectiveness of the FP-AF program as seen from clinical, patient, relatives, psychological, organizational, and economic perspectives.

## Discussion

### Telerehabilitation Program

The aim of the study is to test an individualized CTR program for patients with AF. The primary outcome measure is to assess potential changes in QoL among those patients with AF using telerehabilitation. The secondary outcome measures are changes in AF knowledge, changes in anxiety and depression, changes in motivation, the burden of AF, patients’ and relatives’ perspectives and experiences, patients’ and relatives’ use of the HeartPortal, perspectives and experiences of HPs, the development of clinical data, and a cost-effectiveness analysis.

CR for patients with AF is a fairly new initiative, and national guidelines for AF CR have only recently been published [8]. In this study, we take this initiative further by examining the potential of a CTR program for patients with AF, as telerehabilitation provides a promising and innovative alternative to conventional rehabilitation. The potential advantage of telerehabilitation is that it can provide easier access to rehabilitation assistance and activities and may therefore be a means of overcoming some of the barriers to participation in CR that have been identified in other cardiac patient groups [45]. Use of telerehabilitation may be especially relevant for patients with AF, as this group is very diverse in terms of the subjective impact of their disease; hence, some patients may not feel the need to attend physical appointments at the clinic, but they may be willing or even positive about participating through digital communication and technology. The digital option offered by telerehabilitation may thus improve their QoL.

The FP-AF program will be tested in a multicenter study in order to increase the validity of the study. The FP-AF program is based upon SDT theory and the exploration of how patients, their relatives, and HPs use the HeartPortal. We will therefore analyze the linkages between motivation and use of the digital platform. In a previous study of patients with heart failure, we have documented that telerehabilitation motivates patients with heart failure just as effectively as conventional rehabilitation and that it does not lead to higher levels of psychological distress [46].

To obtain a more in-depth understanding of how patients, relatives, and HPs perceive CTR, we also plan to conduct qualitative interviews with all groups in order to learn more about how they experience the program as part of their everyday life and work, including their evaluation of the specific modules of the program. Using interviews together with questionnaire data will allow for a more holistic understanding of the usability, effect, and acceptance of the proposed program.

